# Predicting Real-world Hypoglycemia Risk in American Adults With Type 1 or 2 Diabetes Mellitus Prescribed Insulin and/or Secretagogues: Protocol for a Prospective, 12-Wave Internet-Based Panel Survey With Email Support (the iNPHORM [Investigating Novel Predictions of Hypoglycemia Occurrence Using Real-world Models] Study)

**DOI:** 10.2196/33726

**Published:** 2022-02-11

**Keywords:** severe hypoglycemia, nonsevere hypoglycemia, type 1 diabetes mellitus, type 2 diabetes mellitus, real-world, risk model, risk prediction, hypoglycemia, symptom, diabetes, risk, model, protocol, survey, internet survey, adverse event, insulin, secretagogue

## Abstract

**Background:**

Hypoglycemia prognostic models contingent on prospective, self-reported survey data offer a powerful avenue for determining real-world event susceptibility and interventional targets.

**Objective:**

This protocol describes the design and implementation of the 1-year iNPHORM (Investigating Novel Predictions of Hypoglycemia Occurrence Using Real-world Models) study, which aims to measure real-world self-reported severe and nonsevere hypoglycemia incidence (daytime and nocturnal) in American adults with type 1 or 2 diabetes mellitus prescribed insulin and/or secretagogues, and develop and internally validate prognostic models for severe, nonsevere daytime, and nonsevere nocturnal hypoglycemia. As a secondary objective, iNPHORM aims to quantify the effects of different antihyperglycemics on hypoglycemia rates.

**Methods:**

iNPHORM is a prospective, 12-wave internet-based panel survey that was conducted across the United States. Americans (aged 18-90 years) with self-reported type 1 or 2 diabetes mellitus prescribed insulin and/or secretagogues were conveniently sampled via the web from a pre-existing, closed, probability-based internet panel (sample frame). A sample size of 521 baseline responders was calculated for this study. Prospective data on hypoglycemia and potential prognostic factors were self-assessed across 14 closed, fully automated questionnaires (screening, baseline, and 12 monthly follow-ups) that were piloted using semistructured interviews (n=3) before fielding; no face-to-face contact was required as part of the data collection. Participant responses will be analyzed using multivariable count regression and machine learning techniques to develop and internally validate prognostic models for 1-year severe and 30-day nonsevere daytime and nocturnal hypoglycemia. The causal effects of different antihyperglycemics on hypoglycemia rates will also be investigated.

**Results:**

Recruitment and data collection occurred between February 2020 and March 2021 (ethics approval was obtained on December 17, 2019). A total of 1694 participants completed the baseline questionnaire, of whom 1206 (71.19%) were followed up for 12 months. Most follow-up waves (10,470/14,472, 72.35%) were completed, translating to a participation rate of 179% relative to our target sample size. Over 70.98% (856/1206) completed wave 12. Analyses of sample characteristics, quality metrics, and hypoglycemia incidence and prognostication are currently underway with published results anticipated by fall 2022.

**Conclusions:**

iNPHORM is the first hypoglycemia prognostic study in the United States to leverage prospective, longitudinal self-reports. The results will contribute to improved real-world hypoglycemia risk estimation and potentially safer, more effective clinical diabetes management.

**Trial Registration:**

ClinicalTrials.gov NCT04219514; https://clinicaltrials.gov/ct2/show/NCT04219514

**International Registered Report Identifier (IRRID):**

DERR1-10.2196/33726

## Introduction

### Background

Although prognostic models can complement clinical decision-making and risk-tailored interventions [1-5], their performance depends heavily on the attributes of their underlying data sources [6]. The prognostic literature on diabetes-related hypoglycemia—a potentially lethal [7,8] and costly [9-11] side effect of insulin and/or secretagogues—has been dominated by analyses of pre-existing trial [12] or administrative databases [13]. However, these sources poorly represent high-risk diabetes populations [14-18], underestimate up to 95% of hypoglycemia events [14,19,20], and limit substantive evidence on potential predictors [21].

Prospective, web-based survey data, especially when collected anonymously [22], can reveal robust indications of hypoglycemia burden [23-26] routinely unmeasured or uncapturable by other research methods [20]. Such insight could help rectify extant evidence gaps, leading to more valid, real-world event prognostication [27] and, ultimately, targeted, cost-effective strategies that support hypoglycemia prevention in broad clinical contexts.

In 2020, our team launched iNPHORM (Investigating Novel Predictions of Hypoglycemia Occurrence Using Real-world Models)—the first prospective (1-year) survey of hypoglycemia risk in the American public with type 1 diabetes mellitus (T1DM) and type 2 diabetes mellitus (T2DM) prescribed insulin and/or secretagogues. The results of this study will culminate in real-world hypoglycemia prognostic models that are readily compatible with and complementary to routine practice. Here, we detail the design and implementation protocol of iNPHORM. The paper has been structured according to established guidelines [28,29] and the CHERRIES (Checklist for Reporting Results of Internet E-Surveys) guidelines [30].

### Objectives of the iNPHORM Study

#### Coprimary Objectives

The primary objectives are as follows:

To determine the real-world incidence of self-reported 1-year severe and 30-day nonsevere daytime and nocturnal hypoglycemia among American adults with T1DM or T2DM prescribed insulin and/or insulin secretagoguesTo develop and internally validate real-world hypoglycemia risk prediction models for 1-year severe, 30-day nonsevere daytime, and 30-day nonsevere nocturnal hypoglycemia, which will be converted into a user-friendly, clinic-based tool

#### Secondary Objective

The secondary objective is to assess treatment-related causes of hypoglycemia among American adults with T1DM or T2DM prescribed insulin and/or insulin secretagogues.

## Methods

### Study Design and Setting

iNPHORM is an internet-based panel survey that was conducted across the United States. Repeated self-assessed measures were taken over 12 monthly interwave intervals via web-based questionnaires. Prospective longitudinality allowed us to (1) obtain data not reliably collected retrospectively or cross-sectionally (eg, variability in totals/averages or low-salience events), (2) assess within-person changes or stability masked by aggregate statistics, and (3) narrow the SE between measurements.

### Participants and Sample Size

Participants were recruited via the web from an established, closed, probability-based internet panel. The internet panel comprised 5 vendor samples of the United States public consenting to receive survey notifications by email (sample frame). Vendor partners used random probability sampling and, when necessary, validity checks, quotas, and multidimensional calibration. These approaches helped maintain fair and representative (geodemographic, attitudinal, and behavioral) sampling within communities [31]. The internet panel comprised >65,000 Americans with self-reported T1DM (N=10,000 approximately) and T2DM (N=58,000 approximately).

Internet panelists could enroll if they were (1) aged 18 to 90 years, (2) living in the United States (past year), (3) self-reporting a diagnosis of T1DM or T2DM [32], and (4) using insulin, secretagogues, or both insulin and secretagogues (past year). Individuals were ineligible if they were unable to read and understand English, possessed insufficient computer and internet literacy, or were participating in a concurrent trial. Those who were pregnant (at screening or in the prior year) and/or those with gestational diabetes were excluded, given their distinct pathogenesis and clinical management.

On the basis of recent conservative techniques [33,34], N≥521 respondents would be required to produce a 25-factor prognostic model for severe hypoglycemia (the rarest event type) with sufficient precision and minimal overfitting with ≤0.05 expected optimism [34,35]. Anticipating a degree of right censoring [35,36], we inflated our target sample to 1250 enrollees.

### Sampling, Recruitment, and Data Collection

Figure 1 summarizes participant sampling, recruitment, and data collection.

**Figure 1 figure1:**
[figure not shown]
Schematic of participant sampling, recruitment, and data collection.

A total of 2 subpanels (*A* and *B*) were recruited into the prospective, 12-wave iNPHORM study using convenience sampling. First, vendor partners emailed a generally worded study invitation to a randomly selected subset of the internet panel (subset A). Those interested were emailed a link to a screener. To enroll, eligible respondents were required to provide consent (see *Ethical Considerations* section), complete a baseline questionnaire (accessible by the emailed link), and register with iNPHORM using a confirmed, valid email address and unique username/password. Enrollees were hosted and monitored by Ipsos Interactive Services (IIS) [37], a global leader in diabetes insights and patient-centered, real-world survey conduct.

Links to the screener and baseline questionnaires remained active until we reached 1250 enrollees (ie, *subpanel A*). Participants in *subpanel A* who failed to complete the first wave follow-up questionnaire were withdrawn and systematically refreshed with new eligible recruits (ie, *subpanel B*). *Subpanel B* was sampled and enrolled in the same way as *subpanel A* but from a different, randomly selected subset (subset B) of the contemporaneous internet panel. Screener and baseline links remained active for approximately 2 weeks or until a 1:1 ratio of *subpanel B* to *subpanel A* wave 1 dropouts was achieved (whichever came first). Collectively, individuals in *subpanel A* who completed the first follow-up questionnaire and all those in *subpanel B* comprised the *iNPHORM longitudinal panel*.

Quota sampling ensured prespecified minimum parameters of the *iNPHORM longitudinal panel*. We required that ≥10% of participants report T1DM, ≥5% are aged ≥75 years, and ≥10% are female/male. Among T2DM respondents, we specified a ≥10% representation for insulin (without secretagogues), secretagogues (without insulin), and a combination of insulin and secretagogue users each.

We followed the *iNPHORM longitudinal panel* for 12 months. The calendar schedule between subpanels was identical; however, systematic refreshment caused follow-up waves to offset by 2 months (*subpanel A*: February 2020 to January 2021; *subpanel B*: April 2020 to March 2021). At each wave, IIS emailed participants an individualized link to a closed, fully automated questionnaire that involved no face-to-face contact. The link could only be accessed by the email recipient using their *iNPHORM longitudinal panel* username/password. Links were active for 7 days from distribution (activation window). The responses were synchronously stored on the IIS platform. Completed questionnaires could not be reaccessed or modified.

### Notifications, Precontacts, and Reminders

Personalized notifications, precontacts, and reminders were emailed automatically by IIS. Each notification contained the questionnaire link, the deadline for submission, and details on remuneration (see *Incentivization Scheme* section). Notifications also included the date of the participant’s last completed questionnaire, as well as their last reported use/type of antihyperglycemic(s) and glucose monitoring device(s).

To boost completion rates [38,39], a precontact alerting participants of an upcoming questionnaire was emailed 7 days before the notification. After the notification, individuals were sent 2 reminder emails on days 4 and 6 of the 7-day activation window. Reminders contained the same information as the corresponding notification emails.

### Incentivization Scheme

Figure 2 summarizes participant honoraria.

**Figure 2 figure2:**
[figure not shown]
Incentivization scheme.

A thank you message and link to a US $10 e-gift card was emailed after each submitted follow-up. At the end of the study, participants received an additional e-gift card of US $30 if they completed any 8 to 11 waves or US $75 if they completed all 12 waves. Wave 6 and 12 responders were entered to win 1 of 3 randomly selected US $500 or US $1000 e-gift cards, respectively.

Incentive amounts balanced our desired response rates against ethical standards of reciprocity [40]. For internet-based surveys, monetary versus other inducements can decrease volunteer bias [35,36] and respondent refusals [41-43]. Lottery incentivization has been shown to act much like cash incentives with a value effect equal to the lottery prize divided by the sample size [44].

### Questionnaire Development Procedures

Western University scientists ([name], [name], and [name]) developed questionnaires in consultation with the literature and pre-existing surveys. Questionnaires were designed in English for use on diverse internet-equipped devices (eg, computers, phones, and tablets). The content was crafted parsimoniously to lessen panel fatigue, conditioning, satisficing, social desirability bias, and demand characteristics [38]. Double-barreled questions, clinical jargon, and value-laden or complex/ambiguous language were avoided. We also ensured that the items were mutually exclusive, exhaustive, and specified an appropriate and consistent level of detail. Key questions were prioritized early; conversely, all sensitive items—justified and respectfully crafted (eg, income was categorized)—were interspersed to encourage respondent honesty [45]. We did not randomize/alternate items within or between questionnaires or participants. When applicable, items addressed the causal ordering of sequence, timing, and duration [46]. Recall intervals balanced the observation probability against the timing of questionnaire completion.

Established design principles were adopted to minimize burden and sustain engagement. Clearly worded preambles signaled topic changes and explained the importance of respondent honesty and vigilance [39,47]. To mitigate comprehension bias, concise instructions and definitions were provided in text and on mouseover [47]. In addition, efforts were taken to enhance accessible visual appeal, navigation, and user convenience. Adaptive questioning streamlined transitions between items and decreased the complexity and length (ie, number of screens) of the web interface questionnaires. For ease of completion, straightforward response options (via radio buttons, checkboxes, drop-down lists, and open-text fields) were presented, and only 1 item appeared per screen. Questionnaires could be accessed, delayed, and/or paused ad libitum up until submission or the activation window closed (whichever came first). Percentage-based progress bars on each screen supplied visual feedback on completion.

Quality assurance methods were applied to reinforce data integrity. *Calibration* questions [48] were incorporated in the screener to detect straight lining, verify item comprehension, and avert nonsensical free text [49]; unsatisfactory answers precluded participant enrollment. In-built logic checks supported data accuracy [49]. For example, questions were prespecified with single- or multi-responses, and *not applicable, prefer not to say*, and *I don’t know* were delimited as exclusive options. Missing responses were immediately flagged. To bypass a question, individuals had to type “OPT OUT” in a pop-up response box, helping discriminate intentional nonresponse from inadvertent omissions/straight lining. At the start of every questionnaire, respondents were reminded to retrieve any documents/materials that could facilitate response accuracy (eg, medication lists/containers and glucose monitoring logs/graphs).

During follow-up, IIS monitored bugs, downtimes, and other unexpected events that could have affected the study design. At any point, participants could email IIS Technical Support (email address was included in all iNPHORM communications).

### Pretesting and Piloting

iNPHORM researchers and colleagues performed extensive pretesting of detailed mock-up and programmed study materials to redress issues of content, display, adaptive questioning, and implementation. Before their dissemination, programmed questionnaires, notifications, and reminders were piloted via in-depth semistructured interviews with 3 participants who were screened and sampled purposively from a subset different than subsets A and B of the internet panel. Of the 3 participants, 1 (33%) participant had T1DM; the other 2 (67%) had T2DM (1, 50%, was prescribed secretagogues without insulin, and 1, 50%, a combination of insulin and secretagogues). A trained IIS moderator ([name]) interviewed participants simultaneously by phone and a computer-assisted personal interview platform using an interview guide developed by the Western University research team.

Qualitative feedback was collected on content, formatting, flow, usability, and technical functionality. Pilot data were also gathered on sample variability, item response rate, and time to completion. Behaviors signaling design issues were documented (eg, instances where the respondent hesitated or requested to change an answer) [38]. Interviews took 60 to 90 minutes. The study materials were emended based on respondents’ feedback. Pilot participants were remunerated US $300 (e-gift card); they were not permitted to enroll in the panel survey.

Once finalized and in field, no changes were made to questionnaires except for the addition of a COVID-19 subquestionnaire (see the *COVID-19 Subquestionnaire* section). Dynamic components were obviated to preserve study replicability.

### Prognostic Factors Related to Hypoglycemia and COVID-19

#### Overview

Across the screener, baseline, and follow-up questionnaires, web-based self-assessed data were collected on a broad scope of hypoglycemia-related anthropometric, demographic, situational or environmental, lifestyle (Multimedia Appendix 1), and clinical (Multimedia Appendix 2 [50-53]) prognostic factors. Follow-up questionnaires also contained items related to COVID-19 (Multimedia Appendix 3; see *Definitions and Measures of Hypoglycemia* section for methods of hypoglycemia-specific data capture).

#### Screener

The pilot screener took an average of 9.6 (SD 4.73; minimum 6 and maximum 15) minutes to complete. Data were collected on age, sex assigned at birth, self-identified gender, residence, concurrent trial involvement, diabetes type, pregnancy status, and insulin and/or secretagogue use (eg, administration mode [when applicable], dose, and duration). Response options for medication type were arranged by class, save second-generation basal insulin analogs, which were listed by brand (Toujeo SoloSTAR, Toujeo Max SoloStar, Tresiba FlexTouch U-100, and Tresiba FlexTouch U-200). Screener data were retained for all consenting individuals.

#### Baseline Questionnaire

On average, pilot respondents completed the baseline questionnaire in 47.3 (SD 13.65; minimum 38 and maximum 63) minutes. Information was elicited on anthropometric, demographic, situational or environmental, and lifestyle factors (eg, levels of aerobic/anaerobic activity and cigarette, alcohol, and recreational drug use). Numerous clinical data were also collected on diabetes duration, diabetes self-management behaviors, diabetes complications (eg, chronic kidney disease), general health status (eg, chronic multi-morbidities and use of dialysis), and health-related quality of life.

To simplify future population-based comparisons and statistical weighting, we devised items with reference to existing population-based surveys by the US Census Bureau (2020) [54] and the Centers for Disease Control and Prevention (ie, National Health and Nutrition Examination [2019-2020] [55], Behavioral Risk Factor Surveillance System [2020] [56], and National Health Interview Survey [2020] [57]). We also embedded several validated questionnaires (eg, Veterans RAND-12 [50,53], Self-Rated Health [51], and Brief Health Literacy Screening Tool [52]).

#### Follow-up Questionnaires

Follow-ups (except wave 6 see *Definitions and Measures of Hypoglycemia* section) were on average piloted in 10.8 (SD 5.30; minimum 7 and maximum 14.5) minutes. Items assessed mutable clinical variables (eg, medication regimen, hemoglobin A1c, and continuous/flash glucose monitoring). Employment status, household income, and health insurance were re-evaluated at waves 4, 8, and 12.

#### COVID-19 Subquestionnaire

Pandemic-related items were added after study commencement in response to the escalating severity of the COVID-19 pandemic. Beginning with *subpanel A* wave 2 (April 21 to April 28, 2020), each follow-up contained a 25-item COVID-19 subquestionnaire that assessed self-reported infection status (per Centers for Disease Control and Prevention’s community case definitions [April 2020]; [58]) and the impact of the pandemic situation on socioeconomic, clinical, and psychosocial aspects of diabetes management [59].

### Definitions and Measures of Hypoglycemia

At baseline and at each follow-up (Multimedia Appendix 4 [60-63]), web-based self-assessed data were collected on severe and nonsevere daytime and nocturnal hypoglycemia; definitions consistent with the 2019 American Diabetes Association Standards of Medical Care in Diabetes [64] were provided in all questionnaires (Textbox 1).

In line with past research [60,65-67], we specified interwaves of ≤1 year for severe and ≤30 days for nonsevere hypoglycemia. At baseline, participants were asked to report on their severe daytime/nocturnal hypoglycemia in the past year and nonsevere daytime/nocturnal hypoglycemia in the past 30 days. To prevent overlapping recall intervals during follow-up, data on nonsevere daytime and nocturnal hypoglycemia were captured *within the past 30 days* (if the last scheduled questionnaire was not completed) or *since the last time an iNPHORM survey was completed* (if the last scheduled questionnaire *was* completed). Given its relative infrequency and saliency, severe daytime and nocturnal hypoglycemia data were captured *since the last time an iNPHORM survey was completed*.

Besides hypoglycemia frequency, closed- and open-ended items assessed event detection methods (eg, symptoms and/or blood glucose), symptom severity (eg, unconsciousness), causes (eg, excess insulin and/or secretagogue use, insufficient carbohydrate intake, and excess physical activity), treatments, hypoglycemia-specific self-management behaviors/social support, and experiences with continuous/flash glucose monitoring. We also investigated the type of assistance required for severe hypoglycemia recovery (eg, treatment by family/friend and health care use). Each month, modified Clarke [61] and Gold [62] scores evaluated impaired hypoglycemia awareness. At wave 6, we administered the Hypoglycemia Fear Survey II [63] and the InHypo-DM Person with Diabetes Questionnaire [60].

iNPHORM (Investigating Novel Predictions of Hypoglycemia Occurrence Using Real-world Models) hypoglycemia definitions provided to participants by severity and timing.

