#### Hypoglycemia Incidence (Coprimary Objective 1)

Crude severe and nonsevere daytime and nocturnal hypoglycemia incidence proportions and densities with 95% CIs for overdispersed count data will be reported overall and by diabetes type, medication regimen, mode of detection (symptoms and/or blood glucose), symptom severity (unconsciousness), and health care use. Incidence density calculations will account for observation durations as an offset for zero-risk and/or unobserved periods.

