### Recruitment Rate

From February 10 to February 25, 2020, 2339 individuals consented to participate in iNPHORM; of these individuals, 1257 (53.74%) completed all actions to enroll (ie, *subpanel A*). Individuals in *subpanel A* who failed to complete wave 1 were withdrawn (488/1257, 38.82%) and systematically refreshed with *subpanel B*. From April 7 to April 23, 3197 individuals consented, of whom 437 (13.67%) were enrolled. Thus, as of April 2020, 1206 participants comprised the *iNPHORM longitudinal panel*.

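### The stated 30-day ceiling on the nonsevere hypoglycemia interval is not met by the survey schedule, and the crude incidence proportion is not stated to allow for this

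*Protocol article*

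**What the plan says.** All references are to the protocol article.

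- *Definitions and Measures of Hypoglycemia*: "we specified interwaves of ≤1 year for severe and ≤30 days for nonsevere hypoglycemia". The same paragraph then sets the follow-up question. If the previous scheduled questionnaire was completed, nonsevere events are reported "since the last time an iNPHORM survey was completed"; if it was missed, they are reported "within the past 30 days".
- *Study Design and Setting*: "Repeated self-assessed measures were taken over 12 monthly interwave intervals".
- *Sampling, Recruitment, and Data Collection*: each wave's link stays open for 7 days. Subpanel A runs from February 2020 to January 2021, and subpanel B follows 2 months later.
- *COVID-19 Subquestionnaire*: the only dated follow-up wave is subpanel A's wave 2, 21 to 28 April 2020.
- *Recruitment Rate*: subpanel A consented from 10 to 25 February 2020 and subpanel B from 7 to 23 April.
- *Coprimary Objectives*: 30-day nonsevere daytime and nocturnal incidence is a coprimary quantity.
- *Hypoglycemia Incidence (Coprimary Objective 1)*: crude incidence proportions and densities are planned. On observation time it says: "Incidence density calculations will account for observation durations as an offset for zero-risk and/or unobserved periods".
- *Model Development*: the nonsevere negative binomial model carries observation duration as an offset.

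**The concern.** A window that opens at the last completed survey and closes whenever the next one is answered has no fixed length. With monthly waves and a week to respond, some windows must exceed 30 days. The first one, from baseline to wave 1, looks longer still, because enrolment closed about four weeks before wave 1 can have opened.

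The chance of reporting at least one event rises with window length. A crude proportion labelled as 30-day incidence would therefore mix windows of different lengths, with the longest concentrated in wave 1. The ceiling is also a stated property of the measurement that readers will rely on when comparing this study with others.

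**Working it through.** **1. Can the ceiling hold at all?** Number the response days 0 to 6 within each 7-day link, and let s be the spacing between wave openings. The window between two consecutive completions is s + b − a, where a and b are the response days, so it ranges from s − 6 to s + 6. A 30-day maximum needs s ≤ 24, which is not monthly.

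**2. What spacing do the dates imply?** The article does not state it. Wave 2 of subpanel A opened on 21 April 2020, so at constant spacing wave 12 opens 10s days later:

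| s (days) | Wave 12 opens |
|---|---|
| 28 | 26 January 2021 |
| 29 | 5 February 2021 |
| 30 | 15 February 2021 |
| 31 | 25 February 2021 |

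Subpanel A is said to end in January 2021. From 21 April 2020 to 31 January 2021 is 285 days, so s is at most 28.5. I use 28.

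**3. Consecutive waves, s = 28.** Windows run 22 to 34 days with mean 28. With uniform response days (assumed), 10 of the 49 combinations of a and b exceed 30 days: 20%.

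**4. Baseline to wave 1, subpanel A, s = 28.** Wave 1 opens on 21 April − 28 days = 24 March 2020 (inferred). Consent dates stand in for baseline completion.

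- From 25 February to 24 March is 28 days; from 10 February it is 43 days. These are the windows if everyone answers on opening day, and 13 of the 16 enrolment dates (81%) already exceed 30.
- Adding response days 0 to 6 gives 28 to 49 days, median 38.5. With uniform enrolment and response, 106 of 112 combinations exceed 30: 95%.
- Counting the closing date as a further response day widens the ranges slightly, to 21–35 days (consecutive) and 28–50 days (wave 1).

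**5. Subpanel B.** Taking the 2-month offset as two 28-day waves, wave 1 opens on 19 May 2020. With enrolment from 7 to 23 April, the window is 26 to 48 days. The offset is rounded, so this shows only that the first interval is probably long here too.

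**6. Effect on the proportion.** Assume negative binomial counts with mean μ per 30 days and dispersion k. Then P(at least 1 in t days) = 1 − (1 + kμt/30)^(−1/k). The article gives no event rates, so μ = 1 and k = 2 are assumptions.

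- At 30 days: 1 − 3^(−1/2) = 0.423.
- Averaged over the windows in step 3: 0.408.
- Averaged over the windows in step 4: 0.469. The wave 1 ratio is 0.469/0.423 = 1.11.
- Wave 1 share of completed waves: at most (1,206 − 193)/10,470 = 1,013/10,470 = 9.7%.
- Pooled: 0.097 × 0.469 + 0.903 × 0.408 = 0.414. The ratio is 0.414/0.423 = 0.98.

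Keeping k = 2 and varying μ from 0.5 to 3, the wave 1 ratio falls from 1.15 to 1.06 and the pooled ratio moves from 0.975 to 0.988. The pooled figure applies subpanel A's wave 1 windows to both subpanels and treats every later record as following a completed wave. Records after a missed wave have a fixed 30-day window, which pulls the ratio towards 1.

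**The case against.** The strongest reply is that little turns on this. The true question rule follows directly after the stated ceiling, so a careful reader knows what was asked. Densities and the nonsevere model allow for duration, so the model behind the tool's 30-day horizon is covered. The pooled proportion moves by about 2%, and no section plans wave-specific proportions. The incidence section neither attaches the 30-day label to the crude proportion nor says how it is formed; an unseen analysis plan may standardise it. The wave 1 date is inferred.

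Most of this stands and limits the size of the point. It does not rescue the ceiling, which fails at any monthly spacing. Nor does it supply an adjustment for the proportion: the one sentence on observation time names densities only, and the 30-day label comes from the coprimary objective itself.

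Two stronger readings do not stand. A reader might assume spacing of 30 or 31 days and infer that later windows stretch further and exceed 30 days much more often. The January 2021 end date for subpanel A does not fit that spacing. A reader might also infer that longer wave 1 windows bring poorer recall, and so a false time trend in daily rates. *Limitations and Strategies to Mitigate Them* puts past-month nonsevere recall at 48% to 75%, but says nothing about whether recall worsens between 28 and 49 days.

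**Conclusion.** The point holds in limited form. The ceiling is wrong as written, whichever monthly spacing applied. At about 28-day spacing, roughly one in five consecutive-wave windows and nearly all of subpanel A's first windows exceed it. These shares rest on an inferred spacing and wave 1 date and on uniform enrolment and response.

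The consequence is confined to the crude incidence proportion for the coprimary 30-day outcome. Under the assumed count distribution it is about 2% low in relative terms when pooled, because later windows average 28 days, and about 11% high for wave 1 alone. This warrants correction because it concerns a coprimary quantity and a stated measurement property. It does not undermine the densities or the prognostic model.

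**What to change.** 1. Replace the 30-day ceiling with a description of the windows as nominally monthly. Give the observed range per record from the completion dates, and note that the first interval is longer. *Notifications, Precontacts, and Reminders* shows that the date of each participant's last completed questionnaire was tracked.
2. Report the 30-day nonsevere incidence proportion as the probability of at least one event in 30 days, from the count model with a log(days) offset, alongside or instead of the crude proportion.
3. Optionally, add a sensitivity analysis that leaves out wave 1.

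The cost is a wording change and one derived estimate from a type of model already planned; no new data are needed. The downside is that the standardised proportion depends on the count model fitting adequately, which is a reason to keep the crude figure beside it. Data collection has ended, so the windows themselves cannot be changed.
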